### **Non-clinical pharmacokinetics**

After entering the body, ansofaxine hydrochloride was rapidly metabolized into ODV. Ansofaxine was nearly undetectable in the blood. After a single dose of ansofaxine hydrochloride (4 - 16 mg/kg in the rats; 10 - 30 mg/kg in the Cynomolgus monkeys) was administered intragastrically, the  $C_{max}$  and AUC of ODV were both positively correlated with the dosages. The rate of drug clearance was similar to what was observed when equal molar doses of ODV were administered intragastrically. No gender differences were seen in the rats or the monkeys.

Compared with PRISTIQ®, the relative bioavailability of ansofaxine hydrochloride extended-release tablets was 131% (calculated based on the measured levels of the metabolite ODV). When equal molar doses of ansofaxine hydrochloride extended-release tablets and solution were

administered to the Cynomolgus monkeys orally, the tablet group showed significantly greater  $t_{1/2}$  and  $T_{max}$  than the solution group, which confirms the slow-release character of the extended-release tablets. The accumulation factor after multiple dosing of ansofaxine hydrochloride extended-release tablets was 1.15, indicating no obvious accumulation of ansofaxine hydrochloride in the body.

After ansofaxine hydrochloride was administered to the rats, both ansofaxine and its metabolite ODV were detectable in tissues. Ansofaxine and ODV were rapidly distributed to a wide range of tissues, but particularly selectively to the target organ inside the brain, hypothalamus ( $C_{\text{hypothalamus}} \gg C_{\text{brain}}$ ). At 0.25 h and 1 h, the concentrations of ansofaxine and ODV in the hypothalamus were comparable. Both ansofaxine and ODV were mostly cleared from all tissues 12 hours after dosing (with concentrations less than 10% of the  $C_{max}$ ), suggesting no obvious accumulation.

The study of ansofaxine hydrochloride metabolism indicated that it is first metabolized into ODV, and then is further metabolized into the same ODV metabolite as previously reported in the literature. No other metabolites were identified.

Ansofaxine hydrochloride showed no obvious inducing effect on hepatic microsomal enzymes CYP1A2, CYP2D6, CYP2C9, CYP3A4 and CYP2C19 in rats. It had no inhibitory effect on human recombinant CYP1A2, CYP 2C9, CYP 2C19, CYP 2D6 and CYP 3A4.

The urinary excretion of ODV reached a plateau 24 hours after ansofaxine hydrochloride was administered to rats (greater than 90% of the total excreted amount in 144 hours). The main excretion routes were urine and feces. About 19.5% ( $\pm 6.8\%$ ) of ODV was excreted in the free form and 75.6% ( $\pm 12.6\%$ ) was excreted in the conjugated form. The total excretion of metabolites in urine and feces was 95.1% ( $\pm 19.6\%$ ).

### Clinical Pharmacology

1. Evaluation of the tolerance and pharmacokinetics of a single oral dose of ansofaxine hydrochloride extended-release tablet in healthy volunteers in a randomized, double-blind, placebo-controlled, dose-escalation study.

72 Male and female health volunteers were recruited in the clinical trial, 60 subjects were treated with an ansofaxine hydrochloride extended-release tablet and 12 subjects were treated with placebo.

In total 72 patients have been evaluated for safety, 14 subjects in ansofaxine hydrochloride extended-release group reported adverse events occurred in 20 times; adverse events including nausea, dizziness, fatigue, diarrhea, ventricular arrhythmia (undiagnosed), sinus tachycardia. Nausea are the most frequently reported AEs. 9 of the incidences adverse events were considered relevant to the investigator drug. The adverse events are mild; clinical or diagnostic observations only; intervention not needed and self-recovered. There are no any new abnormal findings on

physical examination or laboratory or oxygen saturation associated with the investigational drug. In clinical studies, single doses of Ansofaxine hydrochloride extended-release in the range of 20 mg to 200 mg per day shown to be safe and well tolerated.

Single dose, dose ascending of oral administration of ansofaxine hydrochloride extended-release at 20 mg, 40 mg, 80 mg, 120 mg, 160 mg and 200mg, ansofaxine hydrochloride extended-release rapidly converted to active metabolites O-methyl venlafaxine, a very low concentration of drug prototypes can be detected in plasma and urine samples in 80-200mg dose group,

The  $T_{max}$  was 6.00 to 8.00 hours,  $t_{1/2}$  was 8.30 to 11.29 hours,  $C_{max}$  and AUC increased in proportion to the dose, and 50% of ansofaxine hydrochloride were renal elimination in the form of O-methyl venlafaxine.

2. Evaluation of 2- Period, 2 sequence and crossover, comparative pharmacokinetics study of ansofaxine hydrochloride extended-release tablet after fasting and after fed in healthy volunteers

12 Male and female health volunteers were recruited in the clinical trial, 6 male and 6 female. 3 subjects in ansofaxine hydrochloride group reported adverse events occurred in total 5 incidences; described as nausea, 1 adverse events were considered relevant to the investigator drug. The adverse events are mild; clinical or diagnostic observations only; intervention not needed and self-recovered. In clinical study showed well tolerated and safe with single doses of ansofaxine hydrochloride of 120 mg oral administration either with high fat meal or without food.

Oral administration of 120mg ansofaxine hydrochloride with food with higher  $C_{max}$  of Ansofaxine hydrochloride extended-release, later  $T_{max}$  and the bioavailability is about 106% compared to oral administration of ansofaxine hydrochloride without food.

3. Evaluation of the tolerance and pharmacokinetics of single dose vs. multiple doses of ansofaxine hydrochloride extended-release tablet in healthy volunteers in a randomized, double-blind, placebo-controlled, dose-escalation study.

A total of 48 male and female health volunteers were recruited in the clinical trial, 40 subjects were treated with an ansofaxine hydrochloride extended release tablet and 8 subjects were treated with placebo.

In total 48 patients have been evaluated for safety, 15 subjects in ansofaxine hydrochloride extended release group reported adverse events occurred in 24 incidences; 16 of the adverse events were considered relevant to the investigator drug, most common adverse events including nausea 5 incidences, vomiting 3 incidences, diarrhea 3 incidences, and dizziness 2 incidences, laboratory abnormality included elevated of total bilirubin 2 incidences and alanine transaminase 1 incidences. The adverse events are mild; clinical or diagnostic observations only;

intervention not needed and self-recovered. There are no any new abnormal findings on physical examination, 12 lead EKG, laboratory or oxygen saturation associated with the investigational drug. In clinical studies, single doses of ansofaxine hydrochloride extended release in the range of 40 mg to 160 mg per day, once a day for consecutive 7 days shown to be safe and well tolerated.

The results for multiple oral doses of ansofaxine hydrochloride extended-release tablet showed that in a the range of 40-160mg/day, the median  $T_{max}$  was 3-6 hour and the mean  $t_{1/2}$  was 9.09-10.04 hours. The systemic exposure increased slightly in subjects receiving multiple doses. The accumulation factor was 1.20. The plasma levels of ODV reached the steady state after three days of continuous dosing. The steady-state  $C_{max}$  and AUC of ODV were in proportion to the dose.

## Phase II clinical trial

A multicenter, Randomized, Double-Blind, Placebo-Controlled, Parallel Group, Study in major depressive disorder subjects to find the optimal therapeutic dosage, and evaluate the preliminary efficacy and safety of ansofaxine hydrochloride extended-release.

Aged 18-65 years are eligible for the study who met the Diagnostic and Statistical Manual of Mental Disorders (DSM-IV) criteria for major depressive disorder. HAM-D17 total score  $\geq 20$ , Eligible patients will randomly assigned to received ansofaxine hydrochloride extended-release tablet at 40mg, 80mg, 120mg, and 160mg group or placebo- group up to 6 weeks double-blinded treatment, patients will be follow up at week 1, 2, 4, and 6. The primary efficacy measure: the 17 Hamilton Depression Scale (HAM-D17); secondary efficacy measure, the Montgomery-Åsberg Depression Rating Scale (MADRS), Hamilton Anxiety Rating Scale (HAM-A), Clinical Global Impression-severity (CGI-S), The Clinical Global Impressions Scale improvement. HAM-D17 and MADRS response rate and remission. Safety evaluation include assessment of adverse events, vital signs, physical exam, laboratory test, 12-lead ECG, C-SSRS and ASEX etc. Full analysis set will be used to analyse the efficacy of the study.

Result of the study: The primary efficacy measure: HAM-D17 total score change from the baseline. Placebo group:  $-9.71 \pm 6.75$ , Ansofaxine hydrochloride extended-release group (as a treatment group) 40mg:  $-12.53 \pm 5.75$ , 80 mg group:  $-12.84 \pm 6.07$ , 120 mg group:  $-12.14 \pm 7.60$ , 160 mg group:  $-13.56 \pm 5.64$ . The mean differences (90% confidence interval) between each dose group (40 mg, 80 mg, 120 mg and 160 mg) and placebo group were as following: group 40 mg:  $-2.92(-5.05, -0.80)$ , group 80 mg:  $-3.08(-5.19, -0.98)$ , group 120 mg:  $-2.43(-4.53, -0.33)$ , group 160 mg:  $-3.69(-5.82, -1.56)$ : The upper limit of confidence interval is less than 0, indicating that each dose of Ansofaxine hydrochloride extended-release groups were superior to the placebo group.

The secondary efficacy: MADRS total score change from baseline at week 6. Placebo group -  $10.92 \pm 9.38$ , Ansofaxine hydrochloride extended-release 40 mg group  $-15.39 \pm 7.78$ , Ansofaxine hydrochloride extended-release 80 mg group  $-15.30 \pm 8.90$ , Ansofaxine hydrochloride extended-

release 120 mg group  $-15.36 \pm 10.04$ , Ansofaxine hydrochloride extended-release 160 mg group  $-15.65 \pm 7.75$ ; The mean differences (90% confidence interval) between each dose group (40 mg, 80 mg, 120 mg and 160 mg) and placebo group were as following: group 40 mg:  $-4.43(-7.27, -1.59)$ , group 80 mg:  $-3.99(-6.82, -1.17)$ , group 120 mg:  $-3.98(-6.82, -1.15)$ , group 160 mg:  $-4.57(-7.43, -1.72)$ ; the upper limit of confidence interval is less than 0, Ansofaxine hydrochloride extended-release groups were superior to placebo group.

The additional of secondary efficacy endpoint: change from baseline in the Hamilton Anxiety Rating Scale (HAM-A), Anxiety/somatization factor items, Clinical Global Impression-severity (CGI-S), The Clinical Global Impressions Scale improvement, Response rate of 1HAM-D17 and MADRS, and MADRS remission. Each Ansofaxine hydrochloride extended-release groups were superior to placebo group.

The safety efficacy: the adverse events incidences between placebo group and treatment group at dose of 40mg, 80mg, 120mg and 160mg were 61.22 %; 65.38 %; 75 %; 70.59 % and 68.63 % respectively, there was no significant difference between groups, (SS:  $P = 0.6423$ ). The adverse reaction incidences between placebo group and treatment group at dose of 40mg, 80mg, 120mg, and 160mg were 38.78 %, 51.92 %, 65.38 %, 56.86 % and 62.75 %, there was significant difference between groups, ( $P = 0.0630$ ). There was significant difference between groups of ansofaxine hydrochloride extended-release at dose of 80 mg and 160 mg and placebo group ( $P = 0.0097$  and  $P = 0.0272$ ), There was no significant difference between groups of ansofaxine hydrochloride extended-release at dose of 40 mg and 60 mg and placebo group.

Most of adverse events or adverse reaction were mild to moderate, clinical or diagnostic observations only; intervention not needed and self-recovered. Most common adverse events including nausea, decrease appetite, fatigue and dizziness. There were no statistically significant on the Arizona Sex Experience scale and the Columbia-Suicide severity Rating Scale (C-SSRS) between groups at each time point of follow up visit. The most common adverse events associated with drop-out were nausea, headache, and dizziness. Two patients in Ansofaxine hydrochloride extended-release 40mg group were reported to have had severe adverse events: one patient had hypomania and one patient had worsening of the symptoms of depression, both of them were considered relevant to the study drug, follow up to the stable condition. No death occurred in this study.

Phase II clinical trial result showed: The efficacy, safety and tolerability of Ansofaxine hydrochloride extended-release tablets in the range of 40-160 mg superior to the placebo group.

This clinical trial was conducted in accordance with the clinical trial approval issued by the State Food and Drug Administration (CFDA) on June 16, 2015 (Approval No.: 2015L01158/2015L01159/2015L01160/2015L01161).

## 2. Objective:

### The primary objective:

To e verify the efficacy of Ansofaxine hydrochloride extended-release tablets in treatment of major depressive disorder patients.

### The secondary objective:

To valuate the safety of Ansofaxine hydrochloride extended-release tablets in treatment of major depressive disorder patients.

## 3. Study design reference

1. Guidance for developing antidepressant medications(2018) [1]
2. Clinical drug trial registry (2007)
3. Cood Clinical Practice (GCP) (2003)
4. Rational for study of the Ansofaxine hydrochloride extended-release tablet.
5. Pre-clinical pharmacodynamic study of Ansofaxine hydrochloride extended-release tablet
6. Pre-clinical pharmacology and toxicology study of Ansofaxine hydrochloride extended-release tablet
7. CSR of a Randomized, Double-Blind, Placebo-Controlled, Parallel Group, Single Ascending Dose Study in Healthy Subjects to Evaluate the Safety, Tolerability and Pharmacokinetics
8. CSR of two-Period, Parallel Group, Crossover Study to Evaluate the Pharmacokinetics of Ansofaxine hydrochloride extended-release under fed and fast condition in Healthy Subjects
9. CSR of a Randomized, Double-Blind, Placebo-Controlled, Parallel Group, Single and multiple of Ascending Dose Study in Healthy Subjects to Evaluate the Tolerability and Pharmacokinetics
10. CSR of a multicenter, Randomized, Double-Blind, Placebo-Controlled, Parallel Group, dose finding phase II clinical Study to assess the efficacy and safety in major depressive disorder patients .

## 4. Study design

### 4.1 Study methods

A multicenter, Randomized, Double-Blind, Placebo-Controlled phase III clinical Study design to verify the efficacy and safety of ansofaxine hydrochloride extended-release tablets in major depressive disorder.

The study will consist of screening period (0- 7 days), and double blinded treatment period (8 weeks). The first stage is screening period (0-7 days), the second stage is double-blinded treatment period. Eligible subjects will be 1:1:1 randomly assigned to receive Ansofaxine hydrochloride extended-release tablets 80mg, 160mg group or placebo group. All subjects involved with the study will remain blinded to the treatment for 8 weeks. Subjects will be treated accordingly and will follow-up on week 1, 2, 4, 6 and 8.

The primary efficacy endpoint will measure the mean score change from baseline of the Montgomery- Åsberg Depression Rating Scale (MADRS) 10 items.

The secondary efficacy endpoint will measure the mean score change from baseline of the 17 Hamilton Depression Scale (HAM-D17); Clinical Global Impression-severity (CGI-S); Hamilton Anxiety Rating Scale (HAM-A); HAM-D17 response rate and remission rate; MADRS response rate and remission rate; Sheehan disability scale (SDS) and the mean score change of the Clinical Global Impressions-improvement (CGI-I). Safety assessment include adverse events, vital sign, physical exam, laboratory test, 12-lead ECG, The Columbia-Suicide severity Rating Scale (C-SSRS) and Arizona Sex Experience scale (ASEX). [2] .

#### **4.2 Placebo Rational**

Based on 《Guidance on treatment of patients with Major depressive disorder》 (2018), Design for the experimental treatment over placebo to verify the Efficacy and Safety of Ansofaxine hydrochloride extended-release in Major Depressive Disorder. The experiment is placebo-controlled study.

#### **4.3 Dose selection rational**

Phase II clinical trial showed, the efficacy dose were in the range of 40mg/day, 80mg/day, 120mg/day, 160mg/day, of which the overall better effect dose were of the of 80 mg and 160 mg; In addition, based on the recommended dosage of the pristiq® Manual [3], daily dose were 50 mg, but the dosage of 100 mg were also approved. According to the same mole of Venlafaxine (ODV), the 80 mg Ansofaxine hydrochloride extended-release tablets are equivalent to 50 mg pristiq®, 160 mg Ansofaxine hydrochloride extended-release tablets are equivalent to 100 mg pristiq®. Therefore, The Phase III trial study dose is recommended to 80 mg and 160 mg.

#### **4.4 Duration of the study**

From 《Technical guidelines for the clinical trials of antidepressant drugs released》 (2018), The duration of trial is 8 weeks based on the recommendation of 6-8 weeks treatment for acute major depressive disorder.

#### **4.5 Sample size estimate**

Sample size estimate were based on the primary efficacy endpoint, MADRS total score change from baseline, based on phase II clinical trial result, a standard deviation of 9 units was selected based on the MADRS score change from baseline at the end of treatment. Statistically significant

was 5% level on two side with a power of 90%. Active treatment group was significantly different from the placebo group with a mean different of -3.5 units, Subjects were randomly 1:1:1 assigned to 80mg group, 160 group and placebo group. PASS15 software was used to calculate the sample size, 140 patients per group. Considering about 25% drop-out rate, 186 subjects were planned in each group, total 558 subjects in three groups.

#### **4.6 Randomization method**

Dynamic randomization will be applied, the randomization will be conducted by the minimization random allocation system. Pocock&Simon minimization method will be used, baseline MADRS score, age and gender are prognostic factors, and will be taken as stratification factor to make them balance between groups. After qualified subjects recruited, The researcher who involuted in clinical trial will use the specified username and password to log into the system, filled in the screening required information, obtained the random number relevant to certain drug, and then subject will receive the drug based on the randomized number that subject had. The random list will be generated by a third party statisticians using SAS; and the statistician will conduct the procedure of drug blinding set-up and emergency envelope production.

Two copies of randomized drug blinding code shall be kept by the investigator and sponsor for each. The procedure of unblinding will be performed in two levels, first-level unblinding takes place when all data forms have been keyed into the database and database locked, allocation that predetermined by the assignments for each participant who entered into the A, B and C study group are provided, and then statistician will perform the statistical data analysis. Second level of unblinding shall be made after completing the first draft of report of the statistical analysis, and then identify the group A, B and C are corresponded to the study group of 80 mg, 160mg group and placebo group.

#### **4.7 Blind method and design**

This is a double-blind clinical trial. The study drug is produced, packaged and provided by Luye Pharmaceutical Co., Ltd., and the placebo should be in according with the study drug from the appearance, odor and packaging. The third party statistician and other staffs who do not participate in the trial are choosed to do blinding set-up according to the random list; and the blinding set-up procedure will be document.

The third party statistician and the engineer of randomization system who participated in the process of randomization and blinding set-up in the trial shall not be involved in any other work related to the clinical trial and shall not disclose the blinding information to any other staff. Only the encrypted email with blind code message can be send from statistician to the randomization system engineer, and the passwords and encrypted messages shall be transmitted separately.

## 5. Subject selection

### 5.1 Inclusion criteria

- 1) Male or female aged 18 to 65 years subjects from outpatients;
- 2) Subjects currently meet the Diagnostic and Statistical Manual of Manual Disorders, fifth Edition(DSM-5) criteria for MDD with either single or recurrent episodes (296.2/296.3) without psychotic characteristics;
- 3) Subjects has a total score of the Montgomery- Åsberg Depression Scale (MADRS)  $\geq 26$  points at screening;
- 4) Subjects has a clinical Global Impression – severity illness (CGI-S) score  $\geq 4$  points at screening;
- 5) At screening, women of childbearing age (e.g., women who have not undergone surgical sterilization or less than one year after menopause) have a negative pregnancy test result. Male and female subjects of childbearing age agree to take effective contraceptive measures during the entire study period and at least 28 days after the last dose of test drug;
- 6) Subjects voluntarily participate in the trial by signing the informed consent and are able to follow the schedule in the protocol for visits, treatment, laboratory tests and other research procedures.

### 5.2 Exclusion criteria

- (1) Allergic or known to be allergic to venlafaxine and desvenlafaxine;
- (2) Subjects with MDD who were not responsive to the previous venlafaxine treatment with sufficient amount and duration and to at least two different mechanisms of action antidepressants with adequate amount and duration in the past;
- (3) There is a clear suicide attempt or behavior and score of the 10th item (suicidal ideation) in MADRS scale is 4 points or greater;
- (4) Pregnant or lactating women, women who have a planned pregnancy in the near future;
- (5) Subjects meet the diagnostic criteria for other psychotic disorders(except for MDD) in DSM-5, such as Schizophrenia Spectrum and Other Psychotic Disorders, Bipolar and Related Disorders, Obsessive-Compulsive and related Disorders, post-traumatic stress disorder, separation disorders, anorexia nervosa or bulimia and personality disorder;
- (6) Subjects who meet the diagnostic criteria for substance or alcohol abuse (excluding nicotine or caffeine) 6 months prior to the screening;
- (7) MDD secondary to other mental illnesses or physical illnesses;
- (8) Those with a history of seizures (except for convulsions caused by febrile seizures in

children);

(9) Receiving electroconvulsive therapy (ECT) within 3 months prior to screening or according to the investigator's judgment that ECT is currently required;

(10) Those who have received systematic psychotherapy (interpersonal relationship therapy, dynamic therapy, cognitive behavioral therapy) within 3 months of screening;

(11) Those who have received transcranial magnetic stimulation (TMS) 3 months prior to screening;

(12) Those who have received light therapy 2 weeks prior to screening;

(13) Those who have stopped psychotropic drugs for less than 7 half-lives prior to study randomization (monoamine oxidase inhibitor for at least 2 weeks, fluoxetine for at least 1 month);

(14) Those with seriously unstable cardiovascular, liver, kidney, blood, endocrine and other physical diseases or a medical history;

(15) Hypertensive patients with poor blood pressure control ( $SBP \geq 140$  mmHg or  $DBP \geq 90$  mmHg at screening);

(16) There is a history of gastrointestinal disease known to interfere with drug absorption or excretion or a history of surgery known to interfere with drug absorption or excretion;

(17) A history of increased intraocular pressure or narrow-angle glaucoma;

(18) Total bilirubin (TBIL) value is 1.5 times higher, alanine aminotransferase (ALT) or aspartate aminotransferase (AST) is 2 times higher and creatinine (Cr) is 1.2 times higher than the upper limit of normal ranges. Thyroid stimulating hormone (TSH) is outside of the normal range;

(19) Electrocardiogram (ECG) abnormalities are clinically significant at screening and the investigators believe that it is inappropriate for the subjects to be enrolled, such as QTc interval  $>470$  ms for male and QTc interval  $>480$  ms for female;

(20) Those who have participated in other clinical trials within 3 months prior to screening;

(21) Those with serious acute or chronic diseases, mental illnesses or clinically significant abnormalities in laboratory tests, of which investigators believe that the subjects are not suitable for this study.

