## 7.1 Screening

### Visit 1- -7 ~ -1 day

The purpose of the visit was screening whether the patient were eligible for the trial or not. During the time the researcher will screening the candidates:

- Sign informed consent form;
- Baseline demographics (Demographic data will include date of birth, race and height (in cm));
- Medical history taking including but not limited to diagnose of the disorder, date of first diagnosed, histology, prior treatment and medication for other diseases;
- Psychiatric evaluation: MINI-International Neuropsychology Interview (MINI);
- Major Depressive disorder is diagnosed according to the DSM-5 criteria;
- Evaluation: MADRS, CGI-S and C-SSRS;
- Physical examination: including general conditions, skin and mucous, lymph nodes, eyes, ear, nose, mouth, head and neck, thyroid, heart, lung, abdomen, spine, limbs, muscle, joint and nervous system examination;
- Vital signs: body temperature, respiratory rate, pulse and blood pressure (supine position and standing position);
- Height and weight measurement;
- 12-lead ECG examination;
- Laboratory work: including blood routine, urine analysis, blood biochemistry, serology;
- Serology screen: HBsAg, anti-HCV; FT3, FT4, TSH;
- Pregnancy test (only women of childbearing age);
- Confirm the inclusion and exclusion criteria;
- Review concomitant medications;
- Adverse event assessment.

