### **8.2.7 Special precautions and Clinical intervention**

- 1) Deterioration of clinical symptoms and suicide

Major depressive disorder patients at any age, whether or not take antidepressants medication, are possibly to experience the worsening of the depression symptoms, increase the risk to have

suicidal ideation, suicidal attempt or abnormal behavioral changes, the symptoms can persist until a significant remission occurs. It is known that depression per se and certain mental disorders are associated with the risk of suicide, and these mental disorders themselves are the strongest predictors of suicide.

All subjects who treated with the drug (ansofaxine hydrochloride extended-release tablet or placebo) should be closely monitored any sign of deterioration of clinical symptoms, suicidal ideation and attempt and behavioral changes, especially in the early stages of drug therapy. When adults and children who have major depressive disorder, other psychiatric or non-psychiatric disorders treated with antidepressants medications, the following unexpected symptoms may occur: such as anxiety, agitation, panic attacks, insomnia, irritability, hostility, aggression, impulsivity, sedentary (psychomotor restlessness), hypomania and mania. Although the link between the onset of these symptoms and the deterioration of depression and/or suicidal impulses is not yet clear, these symptoms may be a precursor to suicide.

Participants who have continued to deteriorate symptoms of depression, commit suicide or suicidal ideation should consider discontinuing the test drug, especially for those who have serious symptoms, or who have had a sudden onset or new onset of symptoms.

In this trial, participants who have a risk of suicide should be excluded and, on each visit, the Colombian-suicide severity rating Scale (C-SSRS) should be assessed carefully to monitor the risk of suicide.

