| 10. Suicidal ideation
It means that life is worthless, it is better to die, with suicidal thoughts and suicide preparation. The suicide attempt itself does not affect the score. | 0=none
1
2= Tired of life, occasional suicidal thoughts
3
4=I think it might be better to die, often have suicidal thoughts; and think suicide is a kind of
Possible self-solving, but no specific suicide plans and plans
5
6= Have a clear plan to wait for an opportunity to commit suicide; actively prepare for suicide | _ |
| Total score  _                                                                                                                                                                       |                                                                                                                                                                                                                                                                                                                                                   |   |

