**C. Suicide (SUICIDALITY)**

| In the last month: |                                                                  |    | score |     |
|---------------------------|------------------------------------------------------------------|----|--------------|-----|
| C1                        | Do you think it will be better to die or hope that you are dead? | No | Yes          | 1   |
| C2                        | Do you want to hurt yourself?                                    | No | Yes          | 2   |
| C3                        | Do you want to commit suicide?                                   | No | Yes          | 6   |
| C4                        | Do you have a suicide plan?                                      | No | Yes          | 10  |
| C5                        | Are you trying to commit suicide?                                | No | Yes          | 10  |
| In your life:      |                                                                  |    | No           | Yes |
| C6                        | Have you tried suicide?                                          | No | Yes          | 4   |

*Is there at least one of the above codes "yes"?*

*If yes, please assign a score of "Yes" to C1-C6, score according to the score on the right side, and then total the scores. According to the total score, (according to the following criteria):*

|                                 |            |
|---------------------------------|------------|
| No                       | Yes |
| Suicide risk             |            |
| Now suffering            |            |
| Low risk €1-5 points:    |            |
| Medium risk €6-9 points: |            |
| High risk €≥ 10 points   |            |

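### Exclusion criterion 3 joins suicide attempt or behavior to MADRS item 10 ≥4 with *and*; read literally, item 10 ≥4 alone does not exclude, which is narrower than section 8.2.7

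*Protocol*

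**What the plan says.** Criterion 3 in Protocol 5.2, with the same words in the Summary, excludes a patient when: "There is a clear suicide attempt or behavior and score of the 10th item (suicidal ideation) in MADRS scale is 4 points or greater".

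Section 8.2.7, under deterioration and suicide, states the aim more broadly: "In this trial, participants who have a risk of suicide should be excluded".

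Annex 1 anchors a MADRS item 10 score of 4 as "4=I think it might be better to die, often have suicidal thoughts", with suicide seen as a possible way out, "but no specific suicide plans and plans". The same item carries the note "The suicide attempt itself does not affect the score".

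Section 7.1 schedules the MADRS, the C-SSRS and the MINI at screening. No inclusion or exclusion criterion sets a threshold on the C-SSRS or the MINI. Criterion 21 lets the investigator exclude patients judged unsuitable because of serious disease, mental illness or laboratory findings; it does not mention suicide.

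**The concern.** Criterion 3 is the only numbered entry rule that names suicide. Its two parts are joined by *and*, so the ideation threshold does not work as a stand-alone exclusion. A patient who often thinks of suicide but has made no attempt and shown no suicidal behavior would pass it, although 8.2.7 says patients at risk should not enter.

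The setting makes this more than a matter of style. Patients are outpatients, a third are allocated to placebo for 8 weeks (4.1), other antidepressants are prohibited (6.8.1), and there is no data monitoring committee (11.2.2.9). The entry rule would also be looser than the rules for staying in. A suicide attempt during the trial is by itself a ground for withdrawal (5.4.1, item 5), and 8.2.7 asks that stopping the drug be considered when suicidal ideation appears. Section 5.3 removes enrolled subjects found to have met an exclusion criterion, so the same unclear sentence would also govern removal.

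**Working it through.** No formula or plan figure is involved, so the check is a truth table. Let A = clear suicide attempt, B = suicidal behavior, C = MADRS item 10 of 4 or more. The sentence has the form *A or B and C*. It can be grouped literally in two ways. A third reading takes *and* as joining separate entries in a list, which makes it *or*.

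| A | B | C | (A or B) and C | A or (B and C) | A or B or C |
|---|---|---|---|---|---|
| no | no | no | eligible | eligible | eligible |
| no | no | yes | eligible | eligible | excluded |
| no | yes | no | eligible | eligible | excluded |
| no | yes | yes | excluded | excluded | excluded |
| yes | no | no | eligible | excluded | excluded |
| yes | no | yes | excluded | excluded | excluded |
| yes | yes | no | eligible | excluded | excluded |
| yes | yes | yes | excluded | excluded | excluded |
| **Combinations excluded** | | | **3 of 8** | **5 of 8** | **7 of 8** |

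These are logical combinations, not patient proportions.

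1. *Item 10 ≥4 alone* (row 2) is not excluded under either literal grouping. It is excluded only if *and* is read as *or*.
2. *Attempt with item 10 below 4* (rows 5 and 7) is not excluded under the first grouping, which is the natural one because attempt and behavior read as a single phrase. Under the second grouping the attempt alone excludes.
3. The combination in step 2 can occur, because Annex 1 scores item 10 independently of an attempt.
4. The patient in row 2 is also realistic. The score-4 anchor describes frequent suicidal thoughts without a plan. The gap is clearest at 4 and 5. At 6 the anchor includes active preparation, which the C-SSRS in Annex 6 lists under suicidal behavior, so B may then apply.
5. Set beside 8.2.7, both literal groupings are narrower than the stated aim. Only the third column comes close to it.
6. No other provision closes the gap. The C-SSRS and MINI are collected without a cut-off, criterion 21 is discretionary, and 8.2.7 gives no operational definition of risk.

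**The case against.** The strongest reply is that the sentence is a translation slip and the intended meaning is plain. Criterion 1 (allergy to two named drugs), criterion 5 (a run of diagnoses) and criterion 18 (liver and kidney limits) all use *and* where separate sufficient conditions seem meant. Section 8.2.7 may simply describe what the exclusion list is supposed to do, which would again point to *or*. A rater must score item 10 at screening with a threshold of 4 in view, and few investigators would enroll a patient with frequent suicidal thoughts.

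Much of this stands. The cause is probably translation, and the list-joining reading is available. But usage within the list does not settle the matter: criterion 19 uses *and* as a true conjunction, requiring a clinically significant ECG finding together with the investigator's view that enrollment is inappropriate. Evidence that *or* was meant is a reason to write *or*.

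Three stronger readings are tempting, and the documents do not support them.

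- A reader might infer that the protocol has deliberately settled on a narrow suicide rule, or that sites will in fact diverge. The wording is open to the list reading, and how sites would apply it is conjecture.
- A reader might score such a patient on the MINI suicidality module and quote a risk band. The protocol ties no eligibility decision to that module, and the band depends on an assumed answer to the question "Do you want to commit suicide", which item 10 does not determine.
- A reader might treat the lack of a look-back period as a second defect and borrow the past-6-months column of the screening C-SSRS. The criterion contains no such window and can be read as describing the current state. Adding one could admit a patient with an older attempt who would be excluded under the second grouping or the list reading.

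**Conclusion.** The point holds as a wording defect in operative eligibility text. Under both literal groupings, item 10 ≥4 alone does not exclude; under the natural grouping, neither does an attempt with item 10 below 4. Either way the criterion is narrower than 8.2.7, and nothing else in the protocol restores the difference as a rule rather than as a matter of judgement.

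The number of patients affected cannot be derived, because the protocol gives no distribution of item 10 scores or attempt history at screening. No sample size, power, error rate or analysis changes. The matter is patient safety and consistent entry. The conclusion rests on reading the criterion as written and on taking the score-4 anchor as a risk of suicide in the sense of 8.2.7. Monitoring with the C-SSRS and MADRS at every visit, and withdrawal after an attempt, reduce the consequences after entry but do not decide who may enter.

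**What to change.** In 5.2 and in the Summary, reword criterion 3 so that each condition is sufficient by itself: *a clear suicide attempt or suicidal behavior, or a MADRS item 10 score of 4 or greater*. Bring the eCRF eligibility check into line with it.

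This needs one changed conjunction in two places and one database check. No new assessment is required, because the MADRS and the C-SSRS are already done at screening. The cost is a somewhat smaller eligible pool, of a size the document does not allow to be estimated.
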